# Phase III randomised controlled trial on PSMA PET/CT guided hypofractionated salvage prostate bed radiotherapy of biochemical failure after radical prostatectomy for prostate cancer (PERYTON-trial): study protocol

**DOI:** 10.1186/s12885-022-09493-5

**Published:** 2022-04-15

**Keywords:** Salvage radiotherapy, Biochemical recurrence, Hypofractionation, PSMA PET/CT scan, Prostate cancer, Prostatectomy

## Abstract

**Background:**

Salvage external beam radiotherapy (sEBRT) for patients with a biochemical recurrence (BCR) after radical prostatectomy provides a 5-year biochemical progression-free survival up to 60%. Multiple studies have shown that dose escalation to the primary prostate tumour improves treatment outcome. However, data is lacking on the role of dose escalation in the recurrent salvage setting. The main objective of the PERYTON-trial is to investigate whether treatment outcome of sEBRT for patients with a BCR after prostatectomy can be improved by increasing the biological effective radiation dose using hypofractionation. Moreover, patients will be staged using the PSMA PET/CT scan, which is superior to conventional imaging modalities in detecting oligometastases.

**Methods:**

The PERYTON-study is a prospective multicentre open phase III randomised controlled trial. We aim to include 538 participants (269 participants per treatment arm) with a BCR after prostatectomy, a PSA-value of < 1.0 ng/mL and a recent negative PSMA PET/CT scan. Participants will be randomised in a 1:1 ratio between the conventional fractionated treatment arm (35 × 2 Gy) and the experimental hypofractionated treatment arm (20 × 3 Gy). The primary endpoint is the 5-year progression-free survival after treatment. The secondary endpoints include toxicity, quality of life and disease specific survival.

**Discussion:**

Firstly, the high rate of BCR after sEBRT may be due to the presence of oligometastases, for which local sEBRT is inappropriate. With the use of the PSMA PET/CT before sEBRT, patients with oligometastases will be excluded from intensive local treatment to avoid unnecessary toxicity. Secondly, the currently applied radiation dose for sEBRT may be too low to achieve adequate local control, which may offer opportunity to enhance treatment outcome of sEBRT by increasing the biologically effective radiotherapy dose to the prostate bed.

**Trial registration:**

This study is registered at ClinicalTrials.gov (Identifier: NCT04642027). Registered on 24 November 2020 – Retrospectively registered. The study protocol was approved by the accredited Medical Ethical Committee (METc) of all participating hospitals (date METc review: 23-06-2020, METc registration number: 202000239). Written informed consent will be obtained from all participants.

## Background

According to the Dutch Cancer Registry, prostate cancer (PCa) is the first most diagnosed cancer in men with 12.800 new cases and 2.954 deaths in 2018 in the Netherlands [1]. Radical prostatectomy (RP) as primary treatment provides excellent control in localized PCa. After RP, however, approximately 20-40% of patients will develop a biochemical recurrence (BCR) within 5 years. The site of relapse is predominately local (35 to 54%) [2–4]. The only curative treatment option for BCR after RP is salvage external beam radiation therapy (sEBRT). However, 40-50% of the patients treated with sEBRT develop a secondary BCR [5]. This relatively high percentage of a secondary BCR after sEBRT necessitates the need to improve the treatment outcome of sEBRT and subsequently to reduce the need for more aggressive palliative treatment strategies.

Since the introduction of the prostate-specific membrane antigen (PSMA) positron emission tomography (PET)/computed tomography (CT) scan, the detection of oligometastases at very low prostate specific antigen (PSA) levels has significantly improved [6]. PSMA PET/CT can detect nodal metastases as small as 2.4 mm with up to 80% sensitivity and 97% specificity [7]. Recent studies have demonstrated significant changes (30 to 76%) in management decisions for recurrent PCa by incorporating PSMA-PET/CT in an early stage of BCR after RP [6, 7].

Firstly, the high rate of BCR after sEBRT may be due to the presence of oligometastases, for which local sEBRT is inappropriate. With the use of the PSMA PET/CT before commencing sEBRT, patients with oligometastases will be excluded from intensive local treatment to avoid unnecessary toxicity [7–10]. Furthermore, the absence of active disease on PSMA PET/CT scans is an independent prognostic factor for high response to sEBRT [11]. These findings support applying sEBRT in patients with BCR without evidence of distant metastasis on PSMA-PET/CT scan in whom local recurrence in the prostate bed cannot be detected.

Secondly, the currently applied conventional radiation schedule for local sEBRT may be insufficient. This may offer opportunities to improve biochemical progression-free survival (bPFS) by increasing the biologically effective radiotherapy dose to the prostate bed using hypofractionation. Studies have shown that the α/β-ratio for PCa cells is 1.5 Gy, which is lower than that of surrounding normal tissues [12]. This means that PCa cells are more sensitive to fraction dose than surrounding tissues, which is the rationale for increasing the dose-per-fraction (hypofractionation) instead of the total dose. In doing so, the biological dose to the tumour cells, but not to the surrounding normal tissues (bladder and rectum), is expected to increase. Assuming an α/β of 4 Gy for bladder and rectum, the equivalent dose at 2 Gy (EQD2) of the hypofractionated schedule of 20 × 3 Gy is 70 Gy, which is equal to the 70 Gy in the standard arm [12].

In primary PCa, multiple randomised controlled trials (RCT) have shown non-inferiority of a 20 × 3.0 Gy = 60 Gy schedule over 39 × 2.0 Gy = 78 Gy, confirming its biological equivalence of both schedules regarding oncologic outcome and toxicity [13, 14]. Based on these results, we expect the experimental study regimen (20 × 3 Gy) will be biologically equivalent to 78 Gy: 8 Gy higher than the current standard of 70 Gy standard. Although hypofractionation is standard of care in the primary PCa setting, data on hypofractionated sEBRT are scarce. A recently published systematic review supports the tolerance of hypofractionated sEBRT, but stresses the importance of conducting RCTs comparing hypofractionated with standard fractionated sEBRT [15].

To investigate the potential benefit of hypofractionated sEBRT, we will start a phase III RCT (the PERYTON-trial, ClinicalTrials.gov Identifier: NCT04642027). The aim of the PERYTON-trial is to assess whether a dose escalated hypofractionated regimen will improve the 5-year progression-free survival of sEBRT selected with PSMA PET/CT. Furthermore, we will assess the influence of hypofractionation on toxicity, quality of life (QoL) and survival.

## Methods/design

### Study design

The PERYTON-trial is a prospective multicentre phase III randomised controlled trial. (Fig. 1).

**Figure Fig1:**
[figure not shown]
**Fig. 1** The design of the PERYTON-trial

Participating centres are radiotherapy treatment centres in the Netherlands (updated list available on ClinicalTrials.gov).

All eligible participants will be randomly assigned (1:1) to receive:Current standard: conventional sEBRT, 35 × 2 Gy, biologically equivalent dose: 70 Gy.Experimental arm: hypofractionated sEBRT, 20 × 3 Gy, biologically equivalent dose: 78 Gy.

Participants will be stratified by PSA level (≤0.2 ng/mL vs > 0.2- ≤0.5 ng/mL vs > 0.5- < 1.0 ng/mL) and local recurrence on the PSMA PET/CT (presence versus absence).

### Participants

All patients with a BCR, with a PSA value < 1.0 ng/mL, after radical prostatectomy for PCa and staged using a PSMA PET/CT scan (without any evidence of lymph nodes or distant metastases) are eligible for inclusion. Detailed in-and exclusion criteria are summarized in Table 1.

**Table 1 Tab1:** Inclusion and exclusion criteria of the PERYTON-trial. Patients are eligible if they meet all criteria

Inclusion criteria	Exclusion criteria
• Patients with prostate adenocarcinoma treated with radical prostatectomy; • Tumour stage pT2-4, R0-1, pN0, or cN0, cNx according to the UICC TNM 2009, only with Gleason score available; • A recent PSMA-PET scan (< 60 days) without evidence of lymph nodes or distant metastases; • PSA progression after prostatectomy defined as two consecutive rises with the final PSA > 0.1 ng/mL or 3 consecutive rises. The first value must be measured ≥6 weeks after radical prostatectomy; • PSA at inclusion < 1.0 ng/mL; • WHO performance status 0–2 at inclusion; • Age at inclusion between 18 and 80 years; • Written (signed and dated) informed consent prior to registration.	• Prior pelvic irradiation, (chemo) hormonal therapy or orchiectomy; • Previous or concurrent active invasive cancers, other than superficial non-melanoma skin cancers; • Patients with positive lymph nodes or distant metastases based on the surgical specimen of lymphadenectomy or the following minimum diagnostic workup: PSMA-PET/CT scan, 60 days prior to registration; • Double-sided metallic hip prosthesis; • Inability or unwillingness to understand the information on trial-related topics, to give informed consent or to fill out QoL questionnaires.

### Primary endpoint

The primary endpoint is 5-year progression-free survival (PFS), defined as biochemical progression, clinical progression, loco-regional progression, distant progression or the start with hormonal therapy, whichever occurs first. Biochemical progression will be defined as a PSA value of 0.2 ng/mL higher than the PSA Nadir (defined as the lowest PSA value ≥3 months after completion of treatment). Participants with no change or an increase in PSA level after sEBRT will be defined as non-responders.

### Secondary endpoints

Acute grade ≥ 2 gastrointestinal (GI) and genitourinary (GU) toxicities measured 3 months after treatment using both physician-reported score (Common Terminology Criteria for Adverse Events (CTCAE), version 5.0) and patient-reported questionnaires (RTOG Acute Radiation Morbidity Criteria using adapted RTOG/EORTC acute Radiation Morbidity questionnaires);3- and 5-year late grade ≥ 2 GI and GU toxicities, measured using both physician-reported score (CTCAE version 5.0 criteria) and patient-reported questionnaires (RTOG/EORTC criteria);QoL, using the European Organization for Research and Treatment of Cancer (EORTC) QoL thirty item score questionnaires (QLQ-C30) for health-related QoL and the EORTC QoL prostate carcinoma module (QLQ-PR25) is used;Metastasis-free survival: Randomisation date to the date of metastases reported by imaging;PCa-specific mortality;Overall survival at 5 years from date of randomisation.

### Time schedule

The PERYTON-trial started with patient accrual in September 2020. The follow-up starts from the last treatment day, and the main analysis addressing the primary endpoint (5-year PFS) is planned after 5 years of follow-up (i.e., 5 years since the inclusion of the last participant in the study).

### Radiotherapy

#### Radiation dose in sEBRT

A dose–effect relationship has been reported in sEBRT, indicating a 2.0% improvement in bPFS for each additional Gy [16]. One recent RCT, the SAKK-trial 09/10, compared conventional dose schedule (32 × 2 Gy = 64 Gy) to a dose-escalated schedule (35 × 2 Gy = 70 Gy) and showed that dose-intensified sEBRT was not superior to conventional-dose sEBRT [17]. However, this escalated dose of only 4 Gy in the SAKK-trial is probably too low to improve outcome. Studies on dose escalation in primary PCa radiotherapy reported higher GI toxicity, while hypofractionation is proven effective with comparable acute and late toxicity results [13, 14]. This positive experience with hypofractionated radiotherapy in primary PCa may give the opportunity to apply hypofractionation as a dose escalation technique in sEBRT. Data on hypofractionated sEBRT are scarce with only few non-randomised reports. These reports showed adequate disease control and acceptable rates of acute and late side effects, indicating the need to investigate the role of hypofractionation in sEBRT in an RCT [18–21].

#### Quality assurance

A pre-trial quality assurance (QA) process was undertaken to ensure validity and reliability of radiation therapy treatment data to improve protocol compliance within all including centres within this trial. Completion of the pre-trial QA program is mandatory before a centre can start with accrual. At this moment, 6 centres completed the pre-trial QA program. Analyses of the pre-trial QA showed that the dose constraints of the PERYTON-trial are feasible [22].

#### Preparations and positioning

It is recommended to scan and treat patients with a comfortably full bladder. The use of an endorectal balloon is allowed. Local daily online position verification and correction protocols may be applied, being identical in both treatment arms. The use of feet and knee support is recommended.

#### Delineation

Gross tumour volume (GTV) is defined, if present, as the visible local lesion on planning CT (matched with the positive PSMA PET/CT scan). Clinical target volume (CTV) will be defined by any of the published consensus guidelines such as EORTC [23], RTOG [24] or Wiltshire et al. [25] The planning target volume (PTV) margin is according to the local verification protocol. The organs at risk (OAR) include the bladder, rectum, bilateral femora, penile bulb and the large and small bowel.

#### Planning

Highly conformal treatment techniques are used, i.e., intensity modulated radiation therapy (IMRT) or volumetric modulated arc therapy (VMAT). The prescribed dose to the prostate bed is:

Arm 1: 35 × 2.0 Gy = 70 Gy.Arm 2: 20 × 3.0 Gy = 60 Gy.

If a local recurrence is detected within the prostatic bed on PSMA PET/CT-scan, it is recommended to deliver a boost to the GTV. This boost should consist of:

Arm 1: An equivalent dose of 74 – 78 Gy (concomitant or sequential);Arm 2: An equivalent dose of 62 – 63 Gy (concomitant or sequential).

#### Target coverage

At least 99% of the PTV should receive 95% of the prescribed dose: PTV V95% ≥ 99%. Variation of 4% in the V95% (95-99%) is acceptable if necessary to keep the OAR dose within the protocol constraints. Furthermore, 100% of the CTV should receive 95% of the prescribed dose: CTV V95% = 100%.

### Organ at risk constraints

All OAR constraints are summarized in Table 2. A variation of ≤5% of rectal and bladder volumes exceeding the protocol dose constraints are accepted, if needed to reach an acceptable target coverage. The acceptance of rectal volumes beyond this additional 5% of the constraints will be considered a major protocol violation.

**Table 2 Tab2:** Overview of dose constraints to the organs at risk per treatment arm

Organ	Constraints	Arm 1 (35x2Gy)	Arm 2 (20x3Gy)
Rectum	V^a^70	< 5%	
	V65	< 15%	
	V60		< 5%
	V55		< 15%
Rectal wall	V25		< 80%
	V30	< 80%	
	V35		< 50%
	V41	< 50%	
	V50		< 25%
	V60	< 25%	
	Mean Dose	< 30Gy	< 25Gy
Anus	Mean Dose	< 25Gy	<22Gy
Anal wall	V25		< 30%
	V30	< 30%	
Bladder	Dose_0.1cc_	< 105%	< 105%
	V70	< 25%	
	V60	< 50%	< 25%
	V50		< 50%
Femoral head	V45		< 10%
	V55	< 10%	
Penile bulb		ALARA^b^	ALARA

^a^Volume; ^b^As low as reasonably achievable

### Systemic treatment: no androgen deprivation therapy within the PERYTON-study

Two phase III RCTs have shown superior outcomes after postoperative sEBRT when androgen deprivation therapy (ADT) was added (6 months of LHRH-analogues or 24 months of bicalutamide) [26, 27]. However, both trials used low dose sEBRT (64.8 – 66 Gy) and included patients with high PSA levels (2.0 to 4.0 ng/mL). Therefore, the reported benefit of ADT was probably at least partly compensating for low dose sEBRT. Additionally, the benefit was limited to those patients with a high PSA level, so at higher risk for metastases, rather than an additive local benefit. This hypothesis is supported by the use of conventional imaging modalities in both studies to exclude metastases, which could enhance the benefit of ADT in both trials. Post hoc analysis by Shipley et al. showed no benefit of ADT for patients with a PSA level < 0.7 ng/mL [27]. This PSA level will apply to the majority of our population. Using the PSMA PET/CT in an early salvage setting, at low PSA levels of ≤1.0 ng/mL, it is very likely that the use of ADT in the PERYTON-trial will have no added value. In conclusion, the use of ADT is not allowed within the PERYTON-trial.

### Follow-up evaluation

Participants will be followed according to the time schedule in Table 3.

**Table 3 Tab3:** Summary of the follow-up in the first 5 years after RT

Required investigation	Inclusion (within 4 wk. prior to randomisation)	During treatment		Follow-up							
		4 wks	7 wks	1.5 m after RT	3 m after RT	6 m after RT	9 m after RT	12 m after RT	18 m after RT	24 m after RT	Every 12 m (up to 60 m)
Eligibility check	X										
Informed consent	X										
Characteristics	X										
Medical history / medication list	X			X	X	X	X	X	X	X	X
WHO performance status	X			X		X		X	X	X	X
pT-stage and GSS	X										
PSA	X			X	X	X	X	X	X	X	X
Testosterone	X							X		X	X
PSMA/PET CT	X										
Radiotherapy treatment planning		X									
Survival / progression status				X	X	X	X	X	X	X	X
Surveys											
CTCAE v5	X	X^a^		X	X	X	X	X	X	X	X
RTOG-EORTC Toxicity	X	X^a^		X	X	X	X	X	X	X	X
EORTC-QLQ-PR25	X				X	X	X	X	X	X	X
EORTC-QLQ-C30	X					X	X	X	X	X	X
SAE				X	X	X	X	X	X	X	X

^a^Have to be completed at the end of radiotherapy (4 weeks in the experimental arm and 7 weeks in the standard arm)

### Sample size considerations

A systematic review and meta-analysis reported that each additional Gy in the conventional sEBRT-arm is possibly associated with a 2% higher bPFS, independent of other factors. These results imply that our biological dose escalated effect with hypofractionation will result in 16% higher bPFS (8 Gy × 2% per Gy). However, this meta-analysis did not include series using a radiotherapy dose above 70 Gy. In higher dose series as proposed in this study, the relative benefit may be lower and consequently an expected benefit of 16% may be too optimistic. Therefore, a conservative 12% higher 5-year bPFS in the experimental arm of 20 fractions of 3 Gy compared to the conventional sEBRT schedule of 35 fractions of 2 Gy (70 Gy) has been chosen. This estimated benefit of 12% is also supported by a meta-analysis including conventional and hypofractionated regimens addressing the influence of fraction size and the total dose effect on bPFS and toxicity [28].

The results of the GETUG-AFU 16 trial showed a 5-year bPFS of 62% with the conventional fractionated radiotherapy protocol [26]. We used this percentage (62%) for the 5-year bPFS in our conventional sEBRT treatment arm. Following the above mentioned literature, we hypothesize that with the experimental regimen the bPFS can be improved from 62 to 74%. Using an alpha of 5% and a study power of 81%, the required sample size is 235 participants per treatment arm. Assuming a dropout of 12%, we need to recruit 269 participants per treatment arm: 538 in total.

### Statistical analysis

The incidence of progression-free survival will be compared between the two treatment arms using Cox proportional hazards regression analysis to calculate hazard ratios and 95% confidence intervals. Acute and late toxicity rates will be summarized in terms of the proportion of participants in each arm. Log-binominal regression will be used to compare the individual highest grade of acute toxicity and the individual highest grade of late toxicity between both treatment arms. Relative risks will be calculated with 95% confidence intervals. For the analysis of QoL data, a comparison of the change in QoL from baseline level and at different time points will be performed between both treatment arms. The statistical analysis of QoL will be performed by a random effects linear regression model. Stratified randomisation will be taken into account in all analyses by adding the stratification variables to the respective regression models.

In sensitivity analyses, we will repeat all analyses, but with adjustment for potentially prognostic factors (age, pre-operative tumour stage, PSA level, time between radical prostatectomy and biochemical relapse, and comorbidity) or confounding factors (treatment centre).

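### Late toxicity is defined as 3- and 5-year rates but analysed as a crude proportion on one highest grade per man, with no use of follow-up time

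*Protocol article*

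**What the plan says.** All references are to the protocol article.

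- **Secondary endpoints** ties the late harm endpoint to two time points: "3- and 5-year late grade ≥ 2 GI and GU toxicities", scored by physicians (CTCAE) and by patients (RTOG/EORTC).
- **Statistical analysis** gives the summary measure for acute and late toxicity together: "Acute and late toxicity rates will be summarized in terms of the proportion of participants in each arm". For the comparison it says: "Log-binominal regression will be used to compare the individual highest grade of acute toxicity and the individual highest grade of late toxicity". The effect measure follows: "Relative risks will be calculated with 95% confidence intervals".
- The same section uses a time-to-event method for progression-free survival only, which "will be compared between the two treatment arms using Cox proportional hazards regression analysis to calculate hazard ratios and 95% confidence intervals".
- **Follow-up evaluation**, Table 3 ("Summary of the follow-up in the first 5 years after RT"), schedules both toxicity scores at every visit. After the 3-month visit these fall at 6, 9, 12, 18, 24, 36, 48 and 60 months. No stop at progression is stated.
- **Time schedule** places the main analysis at "5 years since the inclusion of the last participant in the study".
- **Sample size considerations** allows for loss: "Assuming a dropout of 12" per cent.

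**The concern.** A plain proportion suits acute toxicity, which is read at 3 months when almost every man is still under observation. Late toxicity accrues over five years, and some men will leave before the end. A proportion has to put those men somewhere: in the denominator as free of toxicity, or out of the analysis. A log-binomial model on one highest grade per man has the same limitation. An estimator that uses the observed time does not force that choice.

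The second difficulty does not depend on dropout. The highest late grade over the whole of follow-up is one value per man, whereas the endpoint asks for a 3-year and a 5-year figure. The article does not say how one becomes two.

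The rationale for hypofractionation is that biological dose rises in tumour but not in bladder and rectum, and the planned interim look covers acute toxicity only. Late GI and GU toxicity is therefore the long-term test of that premise.

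**Working it through.** **The plan's own figure.** The article gives no late-toxicity rate. Its only relevant number is the 12% dropout in the sample size, which reproduces to within one man per arm:

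- Hazard ratio = ln 0.74 / ln 0.62 = 0.630. The Schoenfeld formula with two-sided alpha 0.05 (sidedness is not stated) and power 0.81 gives 151 events.
- 151 / (0.38 + 0.26) = 236 per arm (stated: 235).
- 236 / 0.88 = 268.2, so 269 (stated: 269).

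**Assumptions for the check.** True 5-year late grade ≥ 2 rate F of 10%, 20% or 30%; loss w by 5 years of 12%; constant hazards for toxicity and for loss, independent of each other.

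**Crude 5-year proportion with all men in the denominator:**

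crude = [ln(1−F) / (ln(1−F) + ln(1−w))] × [1 − (1−F)(1−w)]

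For F = 0.20 and w = 0.12: [0.2231 / (0.2231 + 0.1278)] × (1 − 0.80 × 0.88) = 0.6358 × 0.296 = 0.188.

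For 3 years, (1−F)(1−w) is raised to the power 0.6, and the true rate is 1 − (1−F)^0.6.

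| True 5-year rate | Crude 5-year | Shortfall (points) | True 3-year | Crude 3-year |
|---|---|---|---|---|
| 10% | 9.4% | 0.6 | 6.1% | 5.9% |
| 20% | 18.8% | 1.2 | 12.5% | 12.1% |
| 30% | 28.3% | 1.7 | 19.3% | 18.6% |

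**Effect of the denominator, at F = 20% and w = 12%:**

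- All men: 18.8%.
- Only men not lost to follow-up, with random loss: 20%, so no understatement.
- Those men plus men with an event before loss: men lost without an event are (1 − 0.6358) × 0.296 = 0.108, so 0.188 / 0.892 = 21.1%, an overstatement.

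**Relative risk (all men in the denominator):**

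- Equal 12% loss: a true 1.00 stays 1.00, and a true 1.25 stays 1.25.
- Loss of 8% in one arm and 16% in the other, F = 20%: 0.192 / 0.184 = 1.04.
- Loss of 6% and 18%: 0.194 / 0.182 = 1.07.
- These ratios put the arm with less loss on top. If the experimental arm loses more, the ratio of experimental to control becomes 1/1.04 = 0.96 or 1/1.07 = 0.94. For F of 10% to 30% the results are nearly the same.

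**Sampling error for scale.** At 20% in both arms with 269 men each, SE(log RR) = √[2 × 0.8 / (0.2 × 269)] = 0.172. The 95% confidence factor is exp(1.96 × 0.172) = 1.40.

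**The case against.** The design removes most of the problem. Follow-up is a fixed five years, the main analysis waits until five years after the last inclusion, and toxicity is scored to 60 months whether or not a man has progressed. There is therefore little administrative censoring, and a relative risk at a fixed horizon is a legitimate estimator. The 12% is an allowance for the progression comparison, not a forecast of missing toxicity forms. Highest grade could be taken up to 36 and then up to 60 months, and the analysis run twice. Denominator and missing-data rules may stand in the full protocol or the statistical analysis plan, which are not shown.

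Much of this stands, and it limits the size of the point. It does not remove it: the summary and the model are stated choices, they use no follow-up time, and the article does not link one highest grade to two time points.

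Three stronger readings are tempting, and the documents do not support them.

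- **That the rates are understated.** This needs men lost early to be kept as toxicity-free. No denominator is given, and the other conventions give no bias or an upward one.
- **That unequal loss hides harm in the experimental arm.** The article gives no loss by arm. The shift can go either way.
- **That second-line treatment biases the comparison**, because 38% of the control arm and 26% of the experimental arm are expected to progress. Counting all toxicity by randomised arm is a defensible treatment-policy comparison, and the article gives no toxicity rate after progression. Counting toxicity of later treatment would raise the control rate more; stopping the recording at progression, which Table 3 does not say, would lower it more. This is also a separate question from time at risk.

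Nor is it a fault that a man who dies without late toxicity is left without an event: a competing-risk analysis does the same.

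**Conclusion.** The point holds as a mismatch between endpoint and estimator. Late toxicity is specified at 3 and 5 years but analysed with a method that ignores time under observation and yields one value per man.

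The numerical consequence is modest. With all men in the denominator and 12% loss, 5-year rates come out roughly 0.6 to 1.7 points low for true rates of 10% to 30%, and 3-year rates about 0.2 to 0.7 points low. The relative risk is essentially unbiased under equal loss and moves by about 4-7% under the unequal losses assumed, against a 95% confidence factor of about 1.40. The late-toxicity rates, the constant hazards, the independence of loss from toxicity and the loss by arm are all assumptions.

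For a secondary endpoint this is minor to moderate. It is worth correcting because the correction is cheap and the data are already being collected.

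**What to change.** For late toxicity, replace the crude proportion as the main analysis with the cumulative incidence of the first late grade ≥ 2 event at 36 and 60 months:

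- GI and GU separately;
- censoring at the last completed toxicity form, with death as a competing event;
- risk difference and risk ratio between arms at each time point, with 95% confidence intervals, adjusted for the stratification variables (regression on pseudo-values is one way).

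Keep log-binomial regression as planned for acute toxicity. For late toxicity keep it as supportive only, stating the denominator and the cut-off time used for the highest grade.

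The cost is a change of analysis wording and slightly more analysis work. No new data are needed, since grades and visit times come from forms already in Table 3. The reported late rates would be slightly less favourable than crude proportions taken over all men.

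### Acute toxicity is defined at 3 months but analysed as the highest acute grade, and the grade recorded at inclusion is left out of the stated toxicity models

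*Protocol article*

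**What the plan says.** All references are to the protocol article.

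- **Secondary endpoints, acute:** "Acute grade ≥ 2 gastrointestinal (GI) and genitourinary (GU) toxicities measured 3 months after treatment using both physician-reported score", together with patient-reported questionnaires.
- **Secondary endpoints, late:** "3- and 5-year late grade ≥ 2 GI and GU toxicities", on the same two kinds of scale.
- **Statistical analysis, summary:** "Acute and late toxicity rates will be summarized in terms of the proportion of participants in each arm".
- **Statistical analysis, model:** "Log-binominal regression will be used to compare the individual highest grade of acute toxicity and the individual highest grade of late toxicity". Then: "Relative risks will be calculated with 95% confidence intervals". This section repeats neither the grade 2 cut-off nor the 3-month, 3-year and 5-year time points, and does not mention GI and GU separately.
- **Statistical analysis, covariates:** the stratification variables enter all models. Under Study design these are PSA level and local recurrence on PSMA PET/CT. The sensitivity analyses add age, pre-operative tumour stage, PSA level, time from prostatectomy to relapse, comorbidity and centre. Quality of life is compared as change from baseline; for toxicity no baseline is mentioned.
- **Follow-up evaluation, Table 3:** the CTCAE row and the "RTOG-EORTC Toxicity" row are both marked at inclusion, at the end of radiotherapy, at 1.5 and 3 months, and at the later visits.
- **Interim analysis:** toxicity is expected to be equivalent, with perhaps a slight acute increase in the experimental arm because of its shorter treatment time.

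**The concern.** A grade read at one visit and the maximum over several visits are different endpoints. They give different rates and can give different arm comparisons. If the acute excess that the plan anticipates comes early and fades, the highest grade will show it and the 3-month value may not. The trial is open, and having both definitions in the text leaves room to choose between them after results are known.

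The second issue is baseline grade. Every participant has had a radical prostatectomy, so some may have urinary symptoms before irradiation. The grade at inclusion is collected but has no stated role in the toxicity analysis. Nothing stated excludes a grade 2 symptom that was present beforehand and simply persists. If such cases were counted, absolute toxicity rates would be inflated and the relative risk would move towards 1, which is the direction of the plan's own expectation of equivalence.

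**Working it through.** **1. Acute endpoint against acute analysis**

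| | Secondary endpoints | Statistical analysis |
|---|---|---|
| Quantity | grade 2 or worse | highest grade per participant |
| Time | 3 months after treatment | acute period, not delimited |
| Visits in Table 3 | one | end of radiotherapy, 1.5 and 3 months (taking the acute period to end at 3 months) |

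The documents give no visit-specific rates. Assume grade 2 or worse prevalences of 25%, 20% and 10% at the three visits.

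- 3-month endpoint: 10%.
- Highest grade, if the later cases are all among the earlier ones: max(25%, 20%, 10%) = 25%.
- Highest grade, if the visits are independent: 1 − 0.75 × 0.80 × 0.90 = 46%.

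Under these assumptions the two definitions differ by a factor of 2.5 to 4.6.

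**2. Baseline grade**

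The plan states no toxicity rate, toxicity power or baseline prevalence, so there is no toxicity figure to reproduce. The only figure taken from it is 235 per arm (Sample size considerations), used as the number available. That figure reproduces closely. The hazard ratio is ln(0.74)/ln(0.62) = 0.630. Schoenfeld's formula with two-sided 5% alpha and 81% power gives 151 events. The mean event fraction is (0.38 + 0.26)/2 = 0.32, and 151/0.32 = 472, or 236 per arm against 235 stated.

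Let b be the prevalence of grade 2 or worse at inclusion and p the risk of new grade 2 or worse toxicity. If every baseline case persists and is counted, the observed proportion is b + (1 − b)p. Assume p = 20% v 30%, a relative risk of 1.50. Power is for two proportions, two-sided 5%.

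| b | Observed | Difference (points) | RR | Power, all 235 per arm | Power, only men free of grade ≥2 at inclusion (RR 1.50) |
|---|---|---|---|---|---|
| 0% | 20.0% v 30.0% | 10 | 1.50 | 71% | 71% |
| 5% | 24.0% v 33.5% | 9.5 | 1.40 | 62% | 69% |
| 10% | 28.0% v 37.0% | 9 | 1.32 | 55% | 66% |
| 20% | 36.0% v 44.0% | 8 | 1.22 | 42% | 61% |
| 30% | 44.0% v 51.0% | 7 | 1.16 | 33% | 55% |

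Other assumed risks behave alike. For 15% v 25% (RR 1.67), b = 10%, 20% and 30% gives 0.325/0.235 = 1.38, 0.40/0.32 = 1.25 and 0.475/0.405 = 1.17.

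If the true risks are equal, for example 20% v 20%, the observed proportions are equal for every b and the relative risk stays 1.00.

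**3. What a baseline covariate can and cannot do**

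Adjustment handles chance imbalance in baseline grade and can improve precision. It does not by itself undo the dilution. In a Poisson model with a baseline indicator and equal arm sizes at each baseline level, the score equations make the common relative risk equal to the ratio of total events. At b = 20% this is still 0.44/0.36 = 1.22. Counting only grades above the man's own baseline does restore it: if baseline cases persist without worsening, the rates are 0.80 × 20% = 16% and 0.80 × 30% = 24%, and the ratio is 1.50.

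**The case against.** The strongest reply is that a journal article condenses a fuller protocol, and that the derivation of toxicity events, including the handling of baseline, normally sits in the analysis plan. That stands against one tempting inference: that the plan is known to count post-prostatectomy symptoms as radiation toxicity. The text says neither that they count nor that they are excluded. The reply does not reach the covariates, because the article itself lists what enters all models and what enters the sensitivity analyses, and baseline grade is in neither list.

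A reader might also infer that log-binomial regression is the wrong model because a highest grade has several levels. The documents do not support that. With the grade 2 cut-off under Secondary endpoints, and with proportions and relative risks under Statistical analysis, the outcome is binary and the model suits it. The cut-off is merely not repeated.

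Nor is there a clear contradiction for late toxicity. The 3- and 5-year wording can be read as the highest grade up to those times, which fits the analysis. That is an ambiguity to settle. Cumulative incidence with death as a competing event is an option, not a correction.

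For acute toxicity, a charitable reader could take the endpoint to mean the worst grade over the first 3 months. The wording does not say so, and if that is the intent, the repair is the same sentence.

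Finally, the dilution figures rest on assumed rates and on the extreme case in which every baseline case persists and is counted. The absolute difference shrinks much less than the relative risk, from 10 points to between 9.5 and 7. All of this stands.

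**Conclusion.** The point holds in two parts. First, the acute endpoint and its analysis are different quantities within the same article and need to be reconciled. The size of the gap depends on visit-specific rates that are not given; under the assumed prevalences it is 10% against 25% to 46%. Second, a baseline grade that is already collected has no place in the stated toxicity models, although quality of life is analysed against baseline. Using it is a concrete and nearly free improvement.

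The size of any dilution is unknown. The fall from 1.50 to between 1.40 and 1.16 shows direction and possible scale, conditional on the assumed risks, on baseline prevalences of 5% to 30%, and on persistent cases being counted. Randomisation means that no false difference between arms would result if the true rates are equal, so the risk is a real excess looking smaller than it is. The matter concerns secondary endpoints and leaves the primary comparison untouched. It should be corrected before the toxicity data are compared by arm.

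**What to change.** 1. **Acute toxicity.** Use one definition in both sections: highest grade 2 or worse, yes or no, GI and GU separately, over the end of radiotherapy to the 3-month visit. Report 3-month prevalence separately.
2. **Late toxicity.** State it as highest grade 2 or worse up to 3 years and up to 5 years.
3. **Baseline.** Add the inclusion grade on the matching scale and domain as a covariate in the toxicity models. Add an analysis of grade 2 or worse that is also worse than the participant's own inclusion grade; this second step is the one that addresses dilution.
4. **Model.** Keep log-binomial regression, and name Poisson regression with robust variance as the fallback if it does not converge. Non-convergence becomes more likely once baseline grade is included, because men with grade 2 or worse at inclusion may have fitted risks close to 1.

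The cost is a change of wording and slightly more analysis work. Table 3 already schedules every measurement needed, so no visit, form or sample size changes.
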